#### Sampling Procedures

With the exception of Prince Edward Island, each province will have a team of staff responsible for recruitment and data collection. Due to the size and resources in Prince Edward Island, recruitment and data collection will be assigned to the Nova Scotia team. Each provincial research team will create a database of their LTC homes that includes information on each stratum, along with the name and contact information of facility administrators. The stratified proportional random sampling procedure will be performed centrally by a project manager who will then inform provincial teams of the randomly selected LTC homes to recruit. Homes identified in the randomization procedure will be emailed a letter of invitation from the province’s lead investigator and if necessary, a follow-up phone call from a member of the research team. Meetings via Microsoft Teams will be held with homes who express interest in the study. During these meetings, the nature and purpose of the study will be explained along with details of what participation entails. Homes that agree to enroll in the study will be asked to sign a facility agreement form that outlines the expectations of participation. If approval of an operator is required for facility participation the operator is asked to sign an operational approval form prior to the home signing a facility agreement.

Once a home agrees to participate, research staff will conduct orientation meetings (one in-person visit and MS Team or telephone meetings as needed) with administrators and site liaisons to (1) verify the eligible participant pool for completing staff surveys; (2) identify the number and types of care units, staff assignment, and shifts; and (3) discuss the logistics of data collection (eg, dates for data collection, promotion and recruitment strategies, interview flow and schedule, contact information for a site liaison).

### Measures

Data will be collected using TREC’s suite of survey instruments. TREC data collection tools have been administered in Western Canada at several points in time [5,7,18,23] and in Nova Scotia in 2021 with 10 LTC homes [8]. A key component of the surveys is the Alberta Context Tool (ACT), which was developed to measure 10 dimensions of the organization context within health care settings (eg, leadership, culture, feedback, staffing). The ACT contains slight variations for each category of staff and was developed and refined for use in LTC [44]. In addition to the ACT, other surveys will be used to collect data on staff demographics, their perceptions of physical and mental health, well-being, burnout, job satisfaction, as well as missed and rushed care. Permission to access and use these tools has been obtained. Minor revisions to the survey instruments have been made with permission to reflect Atlantic Canada–specific context (eg, provincial term used for care aides). Details of these tools, including their psychometric properties, are outlined in Multimedia Appendix 2 [29-39].

### Translation

Many of TREC's suite of tools are only available in English, which means they have to be translated to French to accommodate the New Brunswick French LTC homes. The quality of these translations is critical in maintaining the integrity of the data collected, and the comparability of data across provinces. The TREC research team has a preexisting rigorous translation protocol that was modified by Hoben et al [45] and is based on international best practices [46]. The first step in the process is to identify the proprietary rights of each survey and to establish which tools are available in French. Of the tools in the suite, 6 tools have existing French versions, and 2 of these cannot be altered. We will obtain permission to translate the remaining 6 tools from English to French (Multimedia Appendix 2).

Translation of these 6 tools and the full TREC survey will involve a rigorous systematic process of forward translation from English to French, back translation from French to English, and cognitive debriefing. Once the forward and back translation processes are completed, additional reviewers will examine the changes for accuracy and precision and, if necessary, make recommendations for the final translation.

We will recruit 4 LTC staff members to complete the translated surveys to verify the understanding, clarity, and appropriateness of the items. This step is for language, comprehension, and cultural issues only; these pilot data will not be included in the study’s sample.

Additional translations will also be required for other research materials, such as demographic questionnaires, consent forms, standardized instructions, and explanations of items within individual surveys.

### Data Collection Procedures

Based on TREC’s experience, data to determine care home units for the study and the number of eligible staff will be collected during the initial in-person meeting between a member of the research team and an LTC care home administrator. Data collection for staff will not begin until these data are obtained. Meetings will take approximately 1 hour and will include a tour of the LTC facility and will allow research staff to build a relationship with care home administration.

A staff member at each care home will be designated as the site liaison by the LTC administrator. The site liaison will work with research staff on promotion, participant recruitment, and scheduling of data collection. An individualized data collection schedule will be cocreated for each home that allows for maximum access to eligible staff and minimum disruptions to the home. Data collection will take place during days, evenings, nights, and weekends. Data collection will be scheduled over a 1-week period, but, if necessary, more time will be provided.

Informed consent will be obtained from all staff prior to data collection. Staff survey data will be collected through a self-administered web-based survey or during a structured interview using Microsoft Teams. Regulated staff will be provided with a link to the closed web-based survey and instructed to complete it voluntarily and independently on the web using the Nooro research platform, on which the survey was thoroughly tested by project staff prior to data collection. Codes given to staff can be used to leave and reenter the survey without losing progress; once the survey is submitted, the code can no longer be used to access the survey thus preventing duplicate entries.

Care aides (unregulated staff) will be scheduled to meet in a private and quiet space with a trained data collector via Microsoft Teams. The data collector will administer the surveys using Computer Assisted Personal Interviewing (CAPI) techniques; survey questions will be read to the participant in a structured interview format using standardized language, and the data collector will enter responses directly into the Nooro research platform. In the event of a staff member becoming upset during data collection, interviews will be paused, and a support protocol will be initiated, including the provision of a list of local mental health resources. The variation in data collection procedures between regulated staff and care aides is based on previous feasibility testing conducted by the TREC team which determined structured interviews are more effective than self-administered web-based surveys for care aides and can be conducted in less time [27].

### Facility- and Unit-Level Data

One facility profile survey will be completed for each participating LTC home, and unit profile surveys will be completed for each unit in the LTC home. These surveys collect data such as the size, ownership model, unit information (ie, number and size of resident care units), types of units (eg, dementia and psychiatric), human resources (eg, physicians and nurse practitioners), care staff complement (eg, type and number of staff on each unit on a given shift), quality improvement activities, and access to programs and services. These surveys will be completed by research staff with LTC administrators or their designate (eg, a director of care or unit manager) through Microsoft Teams during or shortly after the staff data collection period.

### Staff Data

Surveys or interviews can be completed during work time and will take approximately 35 minutes. Multimedia Appendix 2 details the measures that will be collected. Survey item totals varied by staff survey type: care aide surveys have 154-169 items depending on responses to adaptive questions and are answered continuously in the interview format; nurse surveys have 207-219 items across 50 pages; allied health surveys have 138-149 items across 37 pages; and manager surveys have 209-229 items across 53 pages. Items or scales were not randomly ordered. Regulated staff completing the web-based survey could review and change their answers if desired before submission. There are no automatic completion checks alerting participants if their web-based survey contains missed items. Data collectors administering the care aide survey are to check for completion, however, it is not obligatory for care aides to answer missing items.

### Data Collector Training

Training will be in accordance with TREC’s training program for quality assurance purposes and to ensure consistency. Data collectors will receive in-depth standardized CAPI and survey interview training, which will be done in collaboration with TREC’s field coordinator and the ARC LTC staff who have experience with implementing the TREC Survey.

Data collectors will participate in 3 training sessions followed by a quality assurance test. The 3 sessions will be 2-3 hours long and delivered in-person or using Microsoft Teams meetings. These web-based sessions will be recorded for onboarding additional staff at later points in time. The sessions will include didactic teaching, group discussion, and survey practice with peers. Topics will include project background, survey overview, CAPI administration, accessing the survey platform, consent process, shift schedules and resources, and strategies for challenging interviews (eg, technology issues, managing participant distress, keeping participants on track). In addition to survey practice during the 3 sessions, data collectors will be instructed to practice on their own or with friends and family.

During the quality assurance testing, each data collector will complete a minimum of 2 surveys. Data collectors must meet all criteria (eg, obtaining proper consent, reading questions verbatim, appropriate use of scales, proper flow, correctly inputting responses, acting professional, answering or navigating participant questions, managing technology issues, managing participant distress, keeping participants on track). If necessary, additional training will be provided to data collectors on an individual basis to ensure they are able to conduct quality interviews meeting all quality assurance criteria.

Upon completion of training, each data collector will complete at least 1 practice interview with an ARC LTC staff member. Data collectors must receive approval from the ARC LTC staff before being cleared to conduct interviews. Ongoing quality assessment will continue throughout the data collection phase to ensure proficiency in administering surveys using CAPI, consistency between data collectors, and consistency across time ensuring high-quality data.

### Ethical Considerations

Ethical approval for this protocol was obtained from the research ethics boards of the academic institutions of each of the investigators. The study was first reviewed and approved by the Research Ethics Board at Mount Saint Vincent University, Nova Scotia (2023-039), and then subsequently reviewed and approved by ethics boards at Dalhousie University, Nova Scotia (2023-6887); University of New Brunswick (2023-133); Memorial University of Newfoundland (2023.212 or 2024.1112); and Health Prince Edward Island (2023-10-19 or 2024-02-12). Care staff participation will be voluntary, and the information collected will be completely confidential. Data collection with care staff will be held in a private location and no names will be stored with study data. Potential participants will be sent a copy of the consent form prior to the interview, and it will be reviewed just prior to initiating an interview. Informed consent including the purpose of the study, approximate length of completion, data storage and privacy, research team, and ability to opt-out at any time prior to survey completion will be obtained prior to starting the survey. After each care aide survey, the data collector will complete an interview checklist which will capture feedback on the interview and rate its quality. Biweekly data quality reports will be compiled and the number of interviews completed and in progress, time to complete interviews, and occurrence and nature of missing data or extreme scores will be reviewed by investigators and staff. Any unexpected issues will be reviewed with data collectors on a regular basis. Data collectors may be observed conducting interviews for ongoing quality assurance purposes. Data are anonymized upon survey entry, and as such, there is no way to identify or remove participants' responses once the survey has been submitted. Study reports at the unit level will only be available if more than 8 staff from the care unit participate; in cases where fewer than 8 staff from 1 care unit participate, reports will only be available at the facility level to protect participants from being identified. No data will be presented unless the cell size is 5 or more. The identities of the LTC homes that participate will also be held in confidence; sites will only be described by their province, size, region, and language. All the data and the results will be kept indefinitely on a secure server in the Health Research Data Repository that resides in the Faculty of Nursing, University of Alberta. The nominated principal investigator [name] is the data custodian for these data. Contingent on subsequent ethics reviews, its access will be highly restricted. The Health Research Data Repository will support storage, data analysis, and access control for all ARC LTC team members and trainees. Research team members may access the data remotely using unique usernames and strong passwords. Users are unable to download any data or access the internet while logged into the repository. Identifiable data and personal information will be stored separately from their deidentified counterparts to ensure participant confidentiality. Any print documents will be stored securely in locked file cabinets by the project lead in each of the provinces. All staff who participate in the study will receive a CAD $10 (US $7.55) coffee gift card as a token of appreciation. These cards will be supplied to the facility liaison who will hand out cards to staff who agree to participate on survey completion. In addition, LTC homes that participate will be provided with a small stipend at the completion of the study to compensate for any work associated with their participation; the stipend will be based on the size of the home (ie, small, medium, or large). All staff will be given an opportunity to obtain a copy of the study’s findings.

### Knowledge Translation

As part of the feedback process, tailored reports will be generated for each individual care home. These care home reports will be shared with the home administrator. Staff participants will be given the opportunity to receive a generalized report on the study’s findings. If they wish to receive results, they will be asked at the end of the survey to provide an email address. Email addresses for feedback purposes will not be linked to any data provided by participants.

### Data Analysis Plan

To assess the quality of work life among staff working in LTC homes in Atlantic Canada, data will be analyzed by home, by province, and in combination to identify and assess associations, interactions, and predictors of health and work-life outcomes. No correction methods will be calculated. Regression analysis and statistical modeling techniques will be used to explain how work environments within LTC homes are impacting the quality of work life and health of staff. For example, is the work environment (an independent variable) correlated with job satisfaction and burnout? In what way do demographic variables, such as age, or English as a second language mediate the effect of work environment on quality of work life and intention to leave? Multimedia Appendix 3 shows the proposed statistical approaches. Multilevel modeling will be conducted to explore the complex interplay among characteristics at the micro (eg, LTC staff), meso (eg, unit and facility), and macro (eg, province) levels and their effects on indicators of quality of work life and health. Early careers researchers, trainees, and knowledge users will be involved in all aspects of data analysis to help build capacity for research in the LTC sector in Atlantic Canada.

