The LTC workforce cares for residents with complex needs, but their work environments are strained by heavy workloads, inadequate resources, and critical staffing shortages [4,5]. The health and well-being of the LTC workforce are critical components of care quality [5], and yet only in the Western Canadian provinces of British Columbia, Alberta, and Manitoba are such data routinely and systematically collected [6]. In Atlantic Canada, no data are available on workforce characteristics or the work experiences of LTC care providers (ie, indicators of health, well-being, or burnout). LTC in Canada is provincially regulated, meaning policies, regulations, and practices differ among provinces; fundamental differences in how LTC is organized between Western provinces and Atlantic Canada influence how staff work and care for residents, including staffing models and ratios, and education and training requirements of staff. While many other Canadian provinces have continuously relied on internationally trained care workers to supplement the domestic workforce, this is a relatively new phenomenon in the Atlantic Canadian provinces of Nova Scotia, Prince Edward Island, Newfoundland and Labrador, and New Brunswick. Chamberlain et al [7] reported in 2018 that only 35% of care aides working in Alberta LTC homes spoke English as a first language in comparison to 95% of LTC care staff in a Nova Scotian 2021 pilot study [8]. Additionally, according to the 2021 census, between 96% to 99% of the population in Nova Scotia, Prince Edward Island, Newfoundland and Labrador spoke English as a first language, and as a bilingual province, nearly 70% of the New Brunswick population spoke English as a first language while the remaining 30% spoke French [9]. While recent efforts from governments in Atlantic Canada to bring internationally educated workers into LTC have been largely deemed successful from a recruitment perspective [10-12], little is known about how the changing composition of the workforce impacts the LTC environment. More specifically, it is unknown if, and to what degree, domestic and international staff feel supported as they adjust to a more diverse workplace. Further, the combined population of all 4 Atlantic provinces is fewer than 2.5 million [13] and far fewer staff are trained internationally. These differences limit the ability to generalize workforce data from the Western provinces to Atlantic Canada.

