## Methods

### Study Design

This is a cross-sectional, multilevel survey study with an integrated knowledge translation approach with knowledge users (ie, representatives from LTC homes, health authorities, provincial ministries, and key sector organizations) embedded throughout the project. We use the Checklist for Reporting Results of Internet E-Surveys (CHERRIES) reporting guidelines for web-based or internet surveys as a framework for our approach [26]. A detailed description using the CHERRIES checklist is present in Multimedia Appendix 1. Our methods are consistent with the established recruitment and data collection protocols used by TREC [23,27] and will enable comparison of data not only across the Atlantic Canadian provinces but also with the Western Canadian provinces.

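### An example question in the Data Analysis Plan casts age and English as a second language as mediators of the work-environment effect, a role these traits cannot have; they can only modify or confound it

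*Protocol article*

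**What the plan says.** The Data Analysis Plan opens by stating that data will be analysed by home, by province and combined "to identify and assess associations, interactions, and predictors of health and work-life outcomes". It then gives two example questions. The first fixes the exposure: "is the work environment (an independent variable) correlated with job satisfaction and burnout". The second asks in what way "demographic variables, such as age, or English as a second language mediate the effect of work environment on quality of work life", and its wording goes on to a second outcome: "mediate the effect of work environment on quality of work life and intention to leave".

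The next sentence points elsewhere for methods: "Multimedia Appendix 3 shows the proposed statistical approaches". That appendix is not shown. Multilevel models at staff, unit or facility, and province level follow. The article defines no mediation model, indirect effect or decomposition. It also names no specific pair of variables for the interactions.

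On design, the Study Design section says: "This is a cross-sectional, multilevel survey study with an integrated knowledge translation approach".

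**The concern.** Mediation means that the exposure changes the mediator and the mediator changes the outcome. Leadership, culture or staffing in a home cannot alter how old a worker is or which language that worker learned first. The first link of the chain is therefore absent for the individual traits that the sentence names.

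Two roles remain. As effect modifiers, the traits would make the association between environment and work life differ across age or language groups. As confounders, they would relate both to the environment that staff report or work in and to the outcome. Each role calls for a different model term from the one the word *mediate* implies. A mediation analysis would take an association produced by confounding, or by who works where, and present it as a pathway through which the environment acts. The article intends its findings to show where the work environment could be improved, and a spurious pathway through language would be poor guidance for that.

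**Working it through.** **Step 1: what the article says about direction.**

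- The Data Analysis Plan makes the work environment the independent variable and age or language the mediator. This needs a path from environment to trait. No section describes one.
- The Theoretical Framing section runs the other way for language: a growing share of staff with English as a second language is given as something that might lead to changes in policy and culture.
- The same section allows two-way influence, but its example is staff well-being, which an environment can change. Age and first language are not of that kind.
- The design is cross-sectional, so no ordering in time is available to support a mediation reading.

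**Step 2: what a mediation product would measure.** The article states no figure to reproduce, so this is an illustration and every effect size is assumed. Let M be a binary trait with prevalence p, and let the trait precede the environment:

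- E = c·M + noise (variance 1)
- Y = 0.3·E + 0.2·M + 0.2·E·M + noise (variance 1)

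E never affects M, so the true indirect effect is zero in every setting. The true interaction is 0.20.

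The usual product of coefficients is a × b, where

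- a = slope of M on E = c·p(1−p) / [1 + c²·p(1−p)]
- b = coefficient of M given E, without the interaction = 0.2 + 0.2·c·(1−p)

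Worked case, p = 0.20 and c = 0.5: a = 0.5 × 0.16 / (1 + 0.25 × 0.16) = 0.08/1.04 = 0.077; b = 0.2 + 0.2 × 0.5 × 0.8 = 0.28; a × b = 0.022.

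Simulated means (N = 2305, the achieved sample in the article's abstract; 400 replicates per setting) agree with the formula to within 0.001:

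| p | c | Apparent indirect effect | Estimated interaction |
|---|---|---|---|
| 0.05 | 0 | 0.000 | 0.200 |
| 0.05 | +0.5 | 0.007 | 0.211 |
| 0.05 | −0.5 | −0.003 | 0.205 |
| 0.20 | 0 | 0.000 | 0.198 |
| 0.20 | +0.5 | 0.022 | 0.199 |
| 0.20 | −0.5 | −0.009 | 0.199 |
| 0.35 | 0 | 0.000 | 0.199 |
| 0.35 | +0.5 | 0.028 | 0.197 |
| 0.35 | −0.5 | −0.014 | 0.198 |

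**Step 3: reading the result.** When trait and environment are unrelated (c = 0), the product is zero although the slope differs by 0.20 between groups, so it misses the modification. When they are related, the product is non-zero and its sign follows c, although no mechanism exists. In the worked case the environment slope is 0.362 without the trait and 0.340 with it. The difference of 0.022 is confounding removed by adjustment. A mediation reading would call it the part of the effect carried by the trait, about 6% (0.022/0.362). The interaction model returns about 0.20 in every row.

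The illustration ignores clustering of staff within 53 homes. That would widen the uncertainty but would not give the product a different meaning.

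**The case against.** The strongest reply is that this is one loosely chosen word in an example. The sentence illustrates and does not specify, no mediation model is defined, and the methods are deferred to an appendix that cannot be seen. The word may simply have been used for moderation.

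Much of that stands, and it limits the point in four ways.

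- A reader might infer that the moderation question goes unanswered. The documents do not support this: the section's opening sentence plans to assess interactions, although it names no pair.
- A reader might infer that the team is committed to a mediation estimand, or that it certainly meant moderation. The article states neither. Moderation is the likelier meaning, but that is an inference.
- The Background section's remark that "it is unknown if, and to what degree, domestic and international staff feel supported as they adjust to a more diverse workplace" shows interest in a changing workforce. It concerns perceived support among domestic and international staff, not first language or mediation, so it is not a second instance of the error.
- At home level, the environment could change the age or language mix of staff through selection and turnover. That is a coherent question, but the sentence is not framed that way, and a single cross-sectional wave would be weak evidence for it.

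What does not stand is the suggestion that nothing needs correcting. The printed sentence assigns these traits a causal role that is wrong as written. An appendix may clarify what is meant, but it does not correct the article. This is a misstatement, not detail left to a fuller plan.

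**Conclusion.** The point holds in a limited form. As written, the example question gives age and first language a mediator role that individual traits fixed outside the work environment cannot have. An analysis that followed it would present confounding or staff composition as mechanism.

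No size can be taken from the article. Under the assumed effects above, the spurious indirect effect runs from −0.014 to +0.028 against a true value of zero. Other assumptions would give other values. The conclusion rests on the meaning of mediation and on reading the traits at the level of the individual worker, not on those numbers.

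Severity is minor to moderate. A reader might take the error to undermine the second aim in Study Purpose and Objectives, which concerns the effects of the work environment on quality of work life. It does not: that aim does not depend on this question, and no stated sample size, model or primary conclusion changes.

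**What to change.** In the Data Analysis Plan, replace *mediate* with *moderate*. State that the question will be examined through work environment × age and work environment × first-language interaction terms in the planned multilevel models, and that age and language otherwise enter as adjustment covariates. Reconcile the sentence with the interactions named at the start of the section and with Multimedia Appendix 3. If mediation is wanted elsewhere, keep it for variables the environment could plausibly change, and state that as an assumption.

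The cost is one sentence and a model term, with no new data. Analysis is already under way according to the Results section, so the change is best made now.

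The downside is precision. Under the same assumed model, ignoring clustering, the standard error of the interaction is √[1/(Np) + 1/(N(1−p))]. With N = 2305:

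- p = 0.05: √(1/115.25 + 1/2189.75) = 0.096, a 95% half-width of about 0.19
- p = 0.20: √(1/461 + 1/1844) = 0.052, about 0.10
- p = 0.35: √(1/806.75 + 1/1498.25) = 0.044, about 0.09

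The lowest setting matches the Nova Scotia pilot cited in the Background section, where 95% of care staff had English as a first language. If few staff have English as a second language, the language interaction will be imprecise and should be reported with its interval, and a non-significant result should not be read as no difference.
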